### Study setting

The VESPEERA programme will be implemented in 25 hospital departments and 115 general practices in 9 predefined geographical areas in the federal state Baden-Wurttemberg in South-Germany. Hospitals sign a participation contract according to §140a SGB V. The intervention region can be expanded if hospitals from other districts are willing to participate. However, hospitals outside the intervention region are not actively invited to participate. A sample of 50 GP-practices within the same federal state but outside the intervention region will serve as control sites for the patient survey.

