### Sample size calculation

Since large-scale implementation of the VESPEERA program in a geographical region was intended, the number of participating GPs and hospitals was not restricted. Based on the number of GP-practices who participate in HzV-Care and the number of GP-practices who participate in the PraCMan programme, a number of 115 GP-practices are expected to participate. An estimation of the patient sample size was made using claims-data and several assumptions for hospitalisation rates, rates for planned and unplanned admissions, rates of patients with a high risk of rehospitalisation as well as drop-out rates. Assumptions were made based on analyses of AOK claims-data. Admissions are expected to be planned and unplanned in 50% of the cases, respectively. 56% of planned admissions are made by a GP and therefore can be included in the VESPEERA programme. 40% of planned admissions are cases that are expected to be treated in a participating hospital department. After discharge, we calculated with a 20% drop-out rate for patients who are transferred into a nursing home, who pass away or who do not seek GP contact after discharge. 60% of discharged patients are expected to have a risk of rehospitalisation (HOSPITAL Score indicating an intermediate or high risk for rehospitalisation). Figure 2 gives an overview on the sample sizes in each study arm. Given the estimated sample size, we can estimate the effect size (based on the hospitalisation rates after the intervention) that can be detected. Based on claims-data different numbers of hospitalisations can be expected for each of the intervention groups. The alpha level is set to 5%. The following power considerations are based on chi square tests (to test for group differences) and adjusted for the hierarchical structure of the data. The implemented models in the primary analysis will most likely lead to even higher power values. However, we consider the hierarchical structure of the data with cases nested in patients nested in hospitals or practices, respectively. A relatively high ICC (0.3) can be expected when considering measurements within patients, however the number of cases per patient will be relatively small (approx. 1.6 cases per patient). The clustering by hospitals or practices is taken into account with an expected number of approx. 540 patients per hospital and a presumed ICC of 0.03, which is a realistic value in health services research [20]. Furthermore, we assume a rate of re-hospitalisations of 23% in the control group. With a power of 80%, the following reductions in each of the intervention groups can be shown: For study arm 1 a sample size of 1905 cases can be expected. Hereby, a reduction of approx. 8% (from 23% to approx. 15%) can be shown. The control group will be matched and, therefore, the sample size will be the same. For study arm 2 when compared to the control group, the same reduction is detectable, as the same number of cases can be expected as in study arm 1. In a last step, both the study arms 3 and 4 are compared to the control group using a level of significance of 2.5%. In study arm 3, we expect a sample size of 3266 and, thus, a reduction of approx. 7% (from 23 to 16%) can be shown. In study arm 4, a sample size of 4899 hospitalizations can be expected which allows to show a reduction of approx. 6% (from 23 to 17%).

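### The detectable reductions of about 8, 7 and 6 points at 80% power do not follow from the cluster size and ICCs printed beside them

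*Protocol article*

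**What the plan says.** The section on sample size calculation in the protocol article describes its method as follows: "The following power considerations are based on chi square tests (to test for group differences) and adjusted for the hierarchical structure of the data". It then lists the inputs:

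- Patient level: an ICC of 0.3, where "the number of cases per patient will be relatively small (approx. 1.6 cases per patient".
- Hospital or practice level: "an expected number of approx. 540 patients per hospital and a presumed ICC of 0.03".
- A control rate of 23%, and matched controls equal in number to each arm.
- Expected cases: 1905 in arm 1 and the same in arm 2, 3266 in arm 3, 4899 in arm 4.
- A significance level of 5% for arms 1 and 2, and 2.5% each for arms 3 and 4.

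The results are introduced with "With a power of 80%, the following reductions in each of the intervention groups can be shown". For arm 1: "Hereby, a reduction of approx. 8% (from 23% to approx. 15%) can be shown". Arm 2 is said to have the same figure, arm 3 a fall from 23% to 16%, and arm 4 a fall from 23% to 17%. The section shows neither a design effect nor an effective sample size. It adds, without a figure, that the models of the primary analysis will probably have higher power.

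**The concern.** A cluster of 540 with an ICC of 0.03 inflates the variance about 17-fold. An arm of 1905 cases is then worth only about 100 to 110 independent ones, too few to show a fall from 23% to 15% with 80% power. Every input to the calculation is printed, so its outputs can be checked directly.

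The thresholds matter for reading the results. Under the testing procedure in the primary analysis section, arm 2 is tested only if arm 1 is significant, and arms 3 and 4 come last. If arm 1 is null, readers will ask what size of effect the trial could have detected, and will take 8 points from this section.

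**Working it through.** **Formulas.** For a two-sided chi-square test with equal groups, control rate p1, intervention rate p2 and mean rate p̄:

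- n = [z(1−α/2)·√(2p̄(1−p̄)) + z(0.80)·√(p1(1−p1)+p2(1−p2))]² / (p1−p2)²
- power = Φ{[(p1−p2)·√n_eff − z(1−α/2)·√(2p̄(1−p̄))] / √(p1(1−p1)+p2(1−p2))}, with n_eff = cases / design effect

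The protocol does not state sidedness; two-sided is assumed. The case numbers are assumed to be net of the 20% drop-out.

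**Step 1. Design effect behind the stated results.** For arm 1 (23% against 15%, α = 5%), n = (1.960×0.5548 + 0.8416×0.5519)²/0.08² = 376 per group without clustering. Dividing the stated cases by this n gives the design effect that the plan's own results imply.

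| Arm | Stated fall from 23% | α | n without clustering | Stated cases | Implied design effect |
|---|---|---|---|---|---|
| 1, 2 | to 15% | 5% | 376 | 1905 | 5.06 |
| 3 | to 16% | 2.5% | 608 | 3266 | 5.37 |
| 4 | to 17% | 2.5% | 844 | 4899 | 5.81 |

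**Step 2. Design effect from the stated inputs.**

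- Patient level: 1 + (1.6−1)×0.3 = 1.18
- Hospital level: 1 + (540−1)×0.03 = 17.17
- Combined: additive 1 + 0.18 + 16.17 = 17.35; product 1.18×17.17 = 20.26

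**Step 3. Power and detectable reduction with the stated inputs.** For arm 1 with the product form, n_eff = 1905/20.26 = 94. The numerator is 0.08×√94 − 1.0874 = −0.312, and power = Φ(−0.312/0.5519) = 29%.

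| Arm | n_eff per group | Power for stated reduction | Reduction detectable at 80% |
|---|---|---|---|
| 1, 2 | 94–110 | 29–33% | 13.8–14.7 points |
| 3 | 161–188 | 26–30% | 11.9–12.7 points |
| 4 | 242–282 | 28–32% | 10.0–10.7 points |

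With the hospital level alone (17.17), power is 33%, 30% and 33%.

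**Step 4. Other readings that keep 540 and 0.03.** None reaches 80%:

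- one-sided testing: 35–45%
- 540 counted as cases instead of patients: 39–43%
- clustering in the intervention arm only: 42–55%
- each stated reduction stretched by half a point for rounding: 30–39%
- fully nested three-level form, 1 + 0.6×0.3 + 1.6×539×0.03 = 27.05: 19–23%

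Ignoring clustering, or using the patient level alone, gives power near 100%, so that does not reproduce the figures either.

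**Step 5. What would reproduce the results.** With 135 patients per cluster and group and ICC 0.03, the additive design effect is 1 + 0.18 + 134×0.03 = 5.20. The detectable reductions are then 8.1, 6.9 and 5.7 points, and power for the stated reductions is 79%, 81% and 85%. If 540 is kept instead, the ICC would have to be about 0.006 to 0.009.

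**The case against.** The strongest reply is that 540 is given per hospital, not per hospital and arm. Each arm is compared with controls separately, so the relevant cluster is the patients of one hospital within one arm. 540/4 = 135, and 135 recovers all three results, which suggests an unreported step and not failed arithmetic. This stands as a possible explanation. But the text states no such split, and an even one fits badly: the arms differ in size, and arms 2 and 4 are treated in non-participating hospitals. Practices offer another route. All arms hold 1905+1905+3266+4899 = 11,975 cases, about 104 for each of 115 practices. That gives (1+103×0.03)×1.18 = 4.83 and power of 82%, 84% and 87%. But the only size printed is 540 per hospital. Either route means that the printed 540 is not the cluster size used.

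A reader might also infer that 540 contradicts the plan's site numbers, since "The VESPEERA programme will be implemented in 25 hospital departments and 115 general practices". Arms 1 and 3, the arms in participating hospitals, hold 5171 cases, or 5171/1.6 = 3232 patients: about 129 per department. But departments are not hospitals, and the number of hospitals is not given. Six hospitals of about 540 patients, with about four departments each, would fit both figures, so a contradiction is not shown. Nor would six hospitals rescue the results. With arm-specific clusters of 198 (arm 1) and 340 (arm 3), power is 60–67% and 39–46%.

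Finally, the primary test is a difference-in-difference interaction with random intercepts, and pre-period data can remove part of the stable variation between hospitals. That is fair, but the protocol does not quantify the gain and presents the 8, 7 and 6 points as results of the adjusted chi-square calculation.

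**Conclusion.** The inputs and outputs printed in the sample size section contradict each other. The inputs give a design effect of 17.4 to 20.3, and the outputs imply 5.1 to 5.8. Taken as printed, the stated reductions have about 26–33% power instead of 80%.

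Two stronger readings are tempting and are not supported:

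- That the trial has 26–33% power. That range is conditional on 540 being the cluster size within every pairwise comparison, on controls clustering in the same way, and on a post-period chi-square test. The document does not show whether the 540, the ICC or the reductions are wrong, and 540 may be a total over arms.
- That the trial's size rests on these thresholds. The section says that the number of practices and hospitals was not restricted. It takes the sample from expected uptake and derives the detectable effect afterwards.

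What needs correcting is the trial's stated sensitivity, against which a null result would be read.

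**What to change.** Replace 540 by the expected number of patients per cluster within each pairwise comparison, and say whether the cluster is the hospital or the practice. For each arm, state the resulting design effect and effective sample size, and restate the detectable reduction or the power so that inputs and outputs agree. Preferably do this for the difference-in-difference interaction that will be tested, counting the pre-period cases. If 540 is a total over arms, say so and show the step to the per-arm size.

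The cost is a recalculation and a revised paragraph. Some stated figures may become less favourable. Recruitment need not change.

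### Equal sizes of 1905 cases for study arms 1 and 2 do not follow from the plan's stated inputs, and the text does not show which of the two is wrong

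*Protocol article*

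**What the plan says.** All the figures stand in the protocol article, Sample size calculation.

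- Planned against unplanned: "Admissions are expected to be planned and unplanned in 50% of the cases, respectively".
- Eligible share of planned admissions: "56% of planned admissions are made by a GP and therefore can be included in the VESPEERA programme".
- Hospital participation: "40% of planned admissions are cases that are expected to be treated in a participating hospital department".
- Drop-out: "After discharge, we calculated with a 20% drop-out rate for patients who are transferred into a nursing home", which also covers deaths and patients who do not return to the GP.
- Arm 1: "For study arm 1 a sample size of 1905 cases can be expected".
- Arm 2: "the same reduction is detectable, as the same number of cases can be expected as in study arm 1".
- Arm 3: "In study arm 3, we expect a sample size of 3266".
- Arm 4: "In study arm 4, a sample size of 4899 hospitalizations can be expected".

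Table 1 (Intervention group) defines arms 1 and 2 as planned admissions to a participating and a non-participating hospital, and arms 3 and 4 as the same pair for unplanned admissions. Under Primary analysis, arm 1 is tested first at 5%. Arm 2 follows at the same level if arm 1 is significant, and arms 3 and 4 come last at 2.5% each.

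**The concern.** If 40% of planned admissions go to participating departments, the arms defined by that distinction should divide 40:60. They divide 50:50. The unplanned arms do divide 40:60, although the text states the 40% for planned admissions only. So the split appears where it is not stated and is absent where it is.

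At stake are the detectable reductions for the first two steps of the testing sequence. The 8 points for arm 2 have no support except that its count equals that of arm 1. Arm 1 matters more: nothing else is tested unless it succeeds, so an overstated arm 1 would make the whole sequence look better powered than it is.

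**Working it through.** **Inputs** (Sample size calculation): planned share 50%; GP-made share of planned 56%; participating share 40%; drop-out 20%; arm sizes 1905, 1905, 3266 and 4899; control rate 23%; power 80%; alpha 5% for arms 1 and 2; matched controls of equal number. The text does not say whether the test is one- or two-sided; I assume two-sided.

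**Step 1. Reproduce the unplanned arms.** 3266 + 4899 = 8165. Then 0.40 × 8165 = 3266 and 0.60 × 8165 = 4899. Both match exactly.

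**Step 2. The planned arms as stated.** 1905 + 1905 = 3810, and 1905/3810 = 50%.

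**Step 3. Reading A: planned admissions not made by a GP are left out.** Arms 3 and 4 are then the whole unplanned half. With a 50:50 split and the same drop-out everywhere, planned cases after drop-out are also 8165.

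- GP-made: 0.56 × 8165 = 4572.
- Arm 1: 0.40 × 4572 = 1829. The stated 1905 is 76 too high.
- Arm 2: 0.60 × 4572 = 2743. The stated 1905 is 838 too low.

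**Step 4. Reading B: those admissions are counted with arms 3 and 4.** The GP-made planned share of all admissions is 0.50 × 0.56 = 28%, and everything else is 72%.

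- All cases after drop-out: 8165/0.72 = 11,340.
- GP-made planned: 0.28 × 11,340 = 3175.
- Arm 1: 0.40 × 3175 = 1270. The stated 1905 is 635 too high.
- Arm 2: 0.60 × 3175 = 1905. This matches the stated figure.

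**Step 5. Can any reading give equal arms of 1905?** Suppose half of the GP-made cases, not 40%, go to participating departments. Reading A then gives 4572/2 = 2286 per arm and Reading B gives 3175/2 = 1588. Holding the stated sum of 3810 and splitting it 40:60 gives 1524 and 2286. None of these is 1905 and 1905.

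**Step 6. Detectable reductions.** For a two-sided comparison of two proportions, cases per group before clustering are

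n = [1.96·√(2·p̄(1−p̄)) + 0.842·√(p₁(1−p₁) + p₂(1−p₂))]² / (p₁−p₂)².

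With p₁ = 0.23, p₂ = 0.15 and p̄ = 0.19, n = (1.087 + 0.464)²/0.0064 = 376. The design effect implied by the plan's own arm 1 figures is 1905/376.3 = 5.06. I hold it fixed so that only the case count changes. I do not rebuild it from the stated ICCs and cluster size, which is a separate question. Solving for p₂:

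| Cases | Cases/5.06 | Detectable change | Reduction (points) |
|---|---|---|---|
| 1270 (arm 1, Reading B) | 251 | 23% to 13.4% | 9.6 |
| 1829 (arm 1, Reading A) | 361 | 23% to 14.8% | 8.15 |
| 1905 (as stated; arm 2, Reading B) | 376 | 23% to 15.0% | 8.0 |
| 2743 (arm 2, Reading A) | 542 | 23% to 16.2% | 6.75 |

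**The case against.** The best defence is that the 40% is stated for all planned admissions, not for those made by a GP. GP-referred patients in the intervention districts might go to participating departments more often, so equal arms are not impossible. Fig. 2, which shows the arm sizes, was not available to me and may contain the missing step. This stands in part: equality as such cannot be ruled out. But it needs a share that the text does not give, and Step 5 shows that an even split yields 2286 or 1588 per arm.

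A second defence is that 1905 can be reached as a 40% share. Cases before drop-out are 8165/0.8 = 10,206, and 10,206 × 0.56 × 0.40/1.2 = 1905. That takes drop-out as division by 1.2 in arm 1 and multiplication by 0.8 in arms 3 and 4, which the text does not say. It would also put arm 2 at 1905 × 1.5 = 2858, so the arms would still be unequal.

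A third is that a larger arm 2 only makes its 8 points conservative. That is true under Reading A. It gives no comfort under Reading B, where arm 2 is right and arm 1 is a third smaller than stated (635/1905).

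Reading B has its own weakness. Table 1 labels arms 3 and 4 unplanned, and the Recruitment section describes post-discharge enrolment only for unplanned stays. Its exact match to arm 2 is suggestive, not proof.

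**Conclusion.** The contradiction stands: 1905 cases in each of arms 1 and 2 do not follow from the stated inputs. Its direction and size are open.

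- Arm 1 is 1829 or 1270, so it is overstated by 76 or 635 cases. Its detectable reduction is about 8.2 or 9.6 points instead of 8.
- Arm 2 is 2743 or 1905, so it is understated by 838 cases or correct. Its detectable reduction is 6.75 or 8 points.

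These figures assume that the 40% applies to GP-made planned admissions, that drop-out is the same in all arms, that arms 3 and 4 are correct as stated, that the test is two-sided, and that the design effect stays at 5.06.

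A reader might infer that arm 2 is certainly short by about 840 to 950 cases (838 in Step 3, or 2858 − 1905 = 953). The article does not support that. Both figures come from readings that leave non-GP planned admissions out of the count, and Reading B reproduces arm 2 without any shortfall. A reader might also infer that recruitment is being steered by wrong targets. The text gives no basis for this either: participation was not capped, the counts are expectations, and the telephone checks under Data collection and management name no numeric target.

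The practical weight is moderate. The point bears on the stated sensitivity of the first two tests, and most on arm 1 as gatekeeper.

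**What to change.** In the Sample size calculation:

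1. State how planned admissions not made by a GP are handled: left out, or counted with arms 3 and 4. If they are counted there, make this agree with the arm labels in Table 1.
2. State whether the 40% applies to all planned admissions or to GP-made ones, and that it is also used for unplanned admissions.
3. Recompute arms 1 and 2 from the stated inputs, or correct the 40% if equal arms are intended.
4. Restate both sizes and both detectable reductions, each from its own count, and check them against Fig. 2.

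The cost is a recalculation and a few sentences. Design, data collection and testing order are unaffected.

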### Intervention group

The VESPEERA programme comprises recommended practices regarding discharge and care management, which is reinforced by laws (§ 11 Abs. 4 SGB V, § 39 Abs. 1a SGB V, § 112 Abs. 2, Satz 5 SGB V). The planned intervention picks up these regulations for optimal care and offers suggestions for their implementation and enhancement. Patients will not be randomly assigned to a study arm, but receive different intervention components based on the point of study enrolment and the patient’s medical need (see Table 1 – adjusted SPIRIT figure).

**Table 1 Tab1:** Intervention components for all study arms

Interventions		*Study arm 1:*planned admission into a participating hospital	*Study arm 2:*planned admission into a non-participating hospital	*Study arm 3:*unplanned admission into a participating hospital	*Study arm 4:* unplanned admission into a non-participating hospital	*Study arm 5:* control group, not participating in VESPEERA
GP-practice	Interventions in the GP-practice before admission: (A) assessment for admission (B) admission letter and patient brochure	X	X			
Hospital	Interventions in the hospital: (C) telephonic discharge conversation (D) determination of HOSPITAL-Score and patient discharge information	X				
GP-practice	Interventions in the general practice after discharge: (E) assessment for planning of follow-up care (F) telephone monitoring, depending on the risk for rehospitalisation	X	X	X	X	

Assessment for Admission (A): Before a planned hospital admission, the VERAH collects patient information on basic data, admission diagnosis, medical history, existing prescriptions, medication plans and other medical information, social, living and legal situation, communication and care needs.

Admission letter and accompanying patient brochure (B): Based on the assessment for admission, an admission letter which also specifies how and when the practice is available by phone for the hospital staff is created. Patients receive a brochure that informs and prepares for the hospital stay.

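### The four arm sizes cannot all follow from the stated admission shares; arms 3 and 4 are about 20% too large relative to arms 1 and 2 as printed

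*Protocol article*

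**What the plan says.** All inputs are in the protocol article, section Sample size calculation, unless another section is named.

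- Admission type: "Admissions are expected to be planned and unplanned in 50% of the cases, respectively".
- Includable planned admissions: "56% of planned admissions are made by a GP and therefore can be included in the VESPEERA programme".
- Hospital split: "40% of planned admissions are cases that are expected to be treated in a participating hospital department".
- Drop-out after discharge: "we calculated with a 20% drop-out rate for patients who are transferred into a nursing home", and also for death or no GP contact.
- Arm 1: "For study arm 1 a sample size of 1905 cases can be expected". For arm 2, "the same number of cases can be expected as in study arm 1".
- Arm 3: 3266 cases, with a detectable fall from 23% to 16%. Arm 4: "In study arm 4, a sample size of 4899 hospitalizations can be expected which allows to show a reduction of approx. 6" per cent (23% to 17%). Both are tested at 2.5% with 80% power.

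Table 1 (section Intervention group) defines arms 3 and 4 by unplanned admission; arm 4, for example, is "unplanned admission into a non-participating hospital". The Recruitment section gives two enrolment routes: before a planned admission, and after discharge from an unplanned stay. The text gives no total number of admissions. Figure 2, which summarises the arm sizes, is not reproduced in the copy reviewed.

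**The concern.** The arm sizes are presented as the product of the listed shares, so their ratios can be checked without knowing the total. Arms 3 and 4 together should exceed arms 1 and 2 together by the ratio of unplanned to includable planned admissions. They exceed them by more than that.

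These sizes carry the power statement for the last confirmatory step, in which arms 3 and 4 are each compared with controls at 2.5%. If the sizes are too large for the arms as defined, the stated detectable reductions are too favourable. If instead the arms contain cases other than unplanned admissions, Table 1 misdescribes the population being tested.

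**Working it through.** **1. Shares implied by the inputs (percentage of all admissions).**
- Includable planned: 50% x 56% = 28% (arms 1 + 2).
- Unplanned: 50% (arms 3 + 4).
- A drop-out rate common to all arms cancels in the ratio. Summing over participating and non-participating hospitals removes the 40/60 split.
- Expected ratio: 50/28 = 1.786.

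**2. Ratio of the printed sizes.**
- Arms 3 + 4: 3266 + 4899 = 8165. Arms 1 + 2: 1905 + 1905 = 3810.
- 8165/3810 = 2.143, and 2.143/1.786 = 1.20.

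**3. Sizes consistent with the inputs.** The 40/60 split is stated for planned admissions only, but 3266/8165 = 0.400 shows that it was used for arms 3 and 4 as well. Three anchors are possible:

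| Anchor | Unplanned cases | Arm 3 | Arm 4 | Printed relative to consistent |
|---|---|---|---|---|
| 1905 in both arms 1 and 2 | 3810/0.56 = 6804 | 2721 | 4082 | +20% |
| 1905 right only for arm 2 (60% share) | 1905/0.60/0.56 = 5670 | 2268 | 3402 | +44% |
| 1905 right only for arm 1 (40% share) | 1905/0.40/0.56 = 8504 | 3402 | 5103 | -4% |

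No row returns 3266 and 4899. Under a 40/60 split arms 1 and 2 cannot be equal either: if arm 1 is 1905, arm 2 is 1905 x 60/40 = 2858; if arm 2 is 1905, arm 1 is 1270.

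**4. Drop-out on one side only.** Applied to arms 1 and 2 alone, the expected ratio is 1.786/0.8 = 2.232. Applied to arms 3 and 4 alone, it is 1.786 x 0.8 = 1.429. Neither is 2.143.

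**5. Patterns that would fit.**
- A total of 11340 with 72% in arms 3 and 4 gives 11340 x 0.72 x 0.40 = 3266, 11340 x 0.72 x 0.60 = 4899 and 11340 x 0.28 x 0.60 = 1905. The 72% would be the 50% unplanned plus the 22% (50% x 44%) that are planned but not made by a GP. This fit makes arm 1 equal to 11340 x 0.28 x 0.40 = 1270, not 1905.
- A total of 13608 split 14/14/24/36% gives 1905, 1905, 3266 and 4899, so it fits all four sizes. It needs 60% in arms 3 and 4 and an even hospital split for arms 1 and 2.

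Neither pattern is stated in the document, and each departs from its inputs.

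**6. Effect on power (two-sided chi-square, equal groups, no continuity correction; sidedness is assumed).**
- Unadjusted n per group at 80% power and alpha 2.5%: 608 for 23% vs 16%, and 844 for 23% vs 17%.
- Design effects implied by the printed sizes: 3266/608 = 5.4 and 4899/844 = 5.8.
- Holding these and using 2721 and 4082 cases, power at 7 and 6 points is about 72% in each arm, and the detectable reductions are 7.6 and 6.5 points.
- Keeping the number of clusters and letting their size fall (ICC 0.03, within-patient factor 1 + 0.6 x 0.3 = 1.18), power is about 78% and the detectable reductions are 7.1 and 6.1 points.

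**7. Check against the stated clustering.** ICC 0.03 with 540 patients per hospital gives 1 + 539 x 0.03 = 17.17; times 1.18 this is 20.3. With that design effect the printed sizes detect about 12.7 and 10.7 points. The consistent sizes of 2721 and 4082 detect about 13.8 and 11.6.

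**The case against.** A reader might infer that arms 3 and 4 were sized on 72% of admissions, and are therefore overstated by 44% with power down to 63%. The documents do not support that as a finding. The 72% is never stated and the total of 11340 is solved backwards. The fit also treats the 1905 printed for arm 1 as arm 2's share. A different split fits all four sizes at least as well. Taking 1905 as printed for arm 1 alone makes arms 3 and 4 slightly too small. The size of the discrepancy, and even its direction, therefore depends on which of arms 1 and 2 is right.

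It can also be said that planned admissions not made through the GP may have been put deliberately in the arms that receive only post-discharge components, since the Intervention group section ties components to the point of enrolment. The case numbers could then be nearer the truth and the fault would lie in the labels. That is possible. It would contradict Table 1, the two routes in the Recruitment section, and the statement that the GP-made 56% are the planned admissions that can be included.

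The power effect is also modest under one natural reading. If fewer cases mean smaller clusters, 7.1 and 6.1 points still round to the stated 7 and 6. Moreover, the printed reductions fail mainly because the stated ICCs and cluster size give a design effect near 20, which is a separate and larger matter. Finally, these are expected counts and not recruitment targets, because participation was not restricted.

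All of this limits the consequence. None of it makes the four sizes agree with the inputs.

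**Conclusion.** The point holds in this form: no single total reproduces all four printed sizes from the stated shares. With both 1905s taken as printed, arms 3 and 4 are about 20% too large relative to arms 1 and 2. The range is from 4% too small to 44% too large, according to which of arms 1 and 2 is correct. This rests on a drop-out rate common to all arms and on the 40/60 split applying to arms 3 and 4. Counting the 22% of planned admissions not made by a GP in these arms is one possible explanation, not an established one.

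The loss of power from 80% to about 72% (or 78%) is conditional on design effects of 5.4 and 5.8, which are inferred from the printed figures and disagree with the stated clustering. It shows the direction and rough size of the effect and is not a firm estimate. The correction is worth making because the sizes support primary comparisons, but it does not threaten the trial.

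**What to change.** State the total number of expected admissions and derive each of the four arm sizes from it with the stated shares. Say whether the 40/60 split and the drop-out apply to every arm, and correct the equality of arms 1 and 2. Arms 3 and 4 should hold unplanned admissions only. If the planned admissions not made by a GP are meant to be in them, relabel arms 3 and 4 in Table 1 and in the multiple-testing paragraph of the Primary analysis section, bring the Recruitment section into line, and define their controls in the same way.

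Then recompute the detectable reductions for all arms with the stated ICCs and cluster size, and print the design effect used. No corrected size should be adopted from this review: 2721 and 4082 follow only if 1905 stands for both planned arms. The cost is a few lines of text and somewhat less favourable stated figures. No extra patients are needed.
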